**Methods:**

This randomized assessor-blind controlled study will enrol MCI patients with and without the *ApoE* ε4 gene (n = 60/60). Sixty subjects with the *ApoE* ε4 gene and 60 subjects without the *ApoE* ε4 gene will be randomly allocated into treatment and control groups in a 1:1 ratio. Intestinal microbiome profiles will be evaluated by 16 S rRNA sequencing of faecal samples and compared between the groups.

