## Methods

### Study design and population

This single-centre, randomized, assessor- and data analyst-blind controlled study will include 2 groups of patients—those with and without *ApoE ε4* gene polymorphism (n = 60/group)—recruited from the outpatient department of Zhejiang Hospital. Each group of patients will be randomly assigned to the acupuncture group or the sham acupuncture group. The study protocol was approved by the Ethics Committee of Zhejiang Hospital (2021-LS-12 K) on January 25, 2021. Each participant and/or their guardian will be informed of the nature of the study by telephone and will be required to sign the informed consent form before enrolment, which will take place from March 2021 to December 2022. Data will be analysed, and the results will be published in 2023. The proposal is depicted in Fig. 1.

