### Sample size estimation

Using GPower 3.1.9.6 to determine the sample size, a single-factor ANOVA was selected for prior analysis at the 4-group level, with a response size of 0.4, a test level of 0.05, a test efficacy of 0.9, a sample size of 96, and a 25% dropout rate. The final sample size was determined to be 120 people, with 30 people in each group, which was similar to that of other studies [20, 26, 27]. The necessary number of participants was recorded at baseline. Before the end of the enrolment period, more patients will be recruited to replace those who were excluded after baseline examinations.

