#### Primary outcome

According to the research objectives, the improvement of cognitive function as assessed by MoCA will be regarded as the main result of the study. The MoCA covers a wide range of cognitive fields, including attention and concentration, executive function, memory, language, visuospatial structure skills, abstract thinking, calculation, and orientation. It is specifically designed to screen for MCI with high sensitivity (80–100%) and purposefulness (50–76%) [31]. The patient’s faeces will be stored in the refrigerator at − 80 °C. 16 S rDNA sequencing will be used to detect the changes in intestinal flora distribution in patients.

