### Data analysis

Measurement data will be expressed as the means ± standard deviations, and count data will be expressed as frequencies. Data will be analysed using SPSS Statistics for Windows v21 (IBM, Armonk, NY, USA). Pearson’s χ2 test or Fisher’s exact test will be used to analyse classified variables. The t test will be used if the normal distribution and homogeneity test are satisfied, and the rank sum test will be used for nonnormality or nonuniformity of variance. The Kruskal‒Wallis test will be used for multigroup comparisons, and the Wilcoxon rank sum test will be used for comparisons between two samples. For repeated measurement data, repeated measurement analysis of variance will be used. For the pairwise comparison of multiple groups of data, the Bonferroni method will be used to adjust the test level.

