## Discussion

MCI is the prophase state of dementia and the key phase for early intervention. At present, there is no drug that can be used in the MCI stage. Acupuncture reflects the value of early intervention in MCI. The purpose of this study is to evaluate the difference in the curative effect of acupuncture on MCI patients with and without the *ApoE ε4* gene polymorphism and to explore the relationship between the acupuncture mechanism and changes in the intestinal flora. We hope to be able to provide assessable biomarkers associated with acupuncture treatment.

*ApoE* ε4 is associated with degeneration of brain capillary pericytes that maintain blood–brain barrier (BBB) integrity [8, 41]. *ApoE* ε4 carriers (ε3/ε4 or ε4/ε4 alleles) are distinguished from noncarriers (ε3/ε3) by BBB breakdown in the hippocampus and medial temporal lobe [8]. Disruption of the gut flora balance in pathogen-free mice has been linked to increased BBB permeability in the embryonic stage of development and in adults [42] as well as central nervous system abnormalities such as cortical myelination, hippocampal neurogenesis, cognitive function, and memory formation [43]. It has been suggested that systemic inflammation induced by compounds secreted by bacteria impairs the BBB and promotes neurodegeneration [44–46]. We hypothesize that specific types of microbiota contribute to *ApoE* ε4-associated breakdown of the BBB in patients with MCI and can serve as biomarkers for progression to AD.

EX-HN1 (Sishencong) and GV20 (Baihui) have the local effect of regulating brain function. Acupoints can regulate the brain network by increasing connections between cognitive-related regions, thereby improving cognitive function in MCI patients [47]. By improving brain function, acupoints further affect the movement, sensation, and secretion of the gastrointestinal tract through the descending pathway of the gut–brain axis and regulate the composition and behaviour of the gut microbiota [48]. The purpose of our research is to elucidate the relationship between acupoints and gut microbiota.

Clinically, acupuncturists treat patients individually based on their symptoms. As the fixed acupuncture program can reduce research deviation and is more conducive to promotion, we selected fixed acupoints.

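### If Bonferroni runs over all pairs of the four arm-by-genotype groups, as its wording implies, the two randomised MoCA contrasts pay for four others, two of them uninterpretable

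*Protocol article*

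**What the plan says.** Three parts of the protocol article bear on this point.

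- **Design.** Sixty *ApoE* ε4 carriers and 60 noncarriers are enrolled. According to Study design and population, "Each group of patients will be randomly assigned to the acupuncture group or the sham acupuncture group". The abstract adds that participants "will be randomly allocated into treatment and control groups in a 1:1 ratio". Arm is therefore randomised within genotype, and genotype is observed.
- **Size.** In Sample size estimation, "a single-factor ANOVA was selected for prior analysis at the 4-group level". The inputs named there are an effect of 0.4, alpha 0.05 and power 0.9; they lead to 96 people, which a 25% allowance for dropout raises to the total. The result: "The final sample size was determined to be 120 people, with 30 people in each group".
- **Multiplicity.** The Data analysis section says "For the pairwise comparison of multiple groups of data, the Bonferroni method will be used to adjust the test level". It gives no list of pairs, divisor or adjusted level. The same section also lists two-sample tests, with no adjustment attached, and repeated-measures analysis of variance, with no factors named.

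On the target, Primary outcome says that "the improvement of cognitive function as assessed by MoCA will be regarded as the main result of the study". The Discussion gives the purpose as to "evaluate the difference in the curative effect of acupuncture on MCI patients with and without the" ε4 polymorphism.

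**The concern.** The only structure of more than two groups in the article is the set of four arm-by-genotype cells. A rule for pairwise comparison of multiple groups, applied literally to that set, covers every pair. That ignores the two-by-two layout created by randomising within genotype.

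Most of the pairs do not estimate an effect of acupuncture. Some compare people who differ in both arm and genotype, and a significant result there would have no clear meaning. Under Bonferroni, each such pair still takes its share of alpha from the comparisons that randomisation protects. At stake are the power of the within-genotype acupuncture contrasts on MoCA and the width of their adjusted intervals.

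**Working it through.** **1. The plan's own figure.** Inputs from Sample size estimation: four groups, f = 0.4 (read as Cohen's f), alpha 0.05, power 0.9. For the omnibus F test the noncentrality is N·f², with 3 and N − 4 degrees of freedom. At N = 92 power is 0.898. At N = 96 the noncentrality is 96 × 0.16 = 15.36 and power is 0.912. So 96 is the smallest balanced total that reaches 0.90, and the figure reproduces. The final total is 96 × 1.25 = 120, or 30 per cell. A 25% loss from 120 leaves 90, or 22.5 per cell. This calculation concerns the omnibus test, not any pair.

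**2. The pairs.** Four cells give 4 × 3 / 2 = 6 pairs:

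| Pair | Differs in | Randomised? |
|---|---|---|
| Acupuncture v sham, carriers | arm | yes |
| Acupuncture v sham, noncarriers | arm | yes |
| Carriers v noncarriers, acupuncture | genotype | no |
| Carriers v noncarriers, sham | genotype | no |
| Acupuncture carriers v sham noncarriers | both | no |
| Sham carriers v acupuncture noncarriers | both | no |

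**3. The level.** All-pairs Bonferroni gives 0.05/6 = 0.00833. The two randomised pairs then use 2 × 0.00833 = 0.0167 of the 0.05, and the other four take 0.0333. A family of two would give 0.05/2 = 0.025 each.

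**4. From f to a difference.** The article gives no pattern of means behind f = 0.4, so d must be assumed. If only the arms differ, and equally in both genotypes, each cell lies 0.4 SD from the grand mean and d = 2 × 0.4 = 0.8. The largest difference between two cells that f = 0.4 allows (the other two midway) is 0.4 × √8 = 1.13. A smaller value, 0.5, is added for range.

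**5. Power per randomised contrast.** Two-sided two-sample t test, noncentrality d·√(n/2), 2n − 2 degrees of freedom. For d = 0.8 the noncentrality is 0.8 × √15 = 3.10 at n = 30 and 0.8 × √11.25 = 2.68 at n = 22.5.

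| n per cell | d | at 0.05/6 | at 0.025 | loss |
|---|---|---|---|---|
| 30 | 0.5 | 0.224 | 0.364 | 0.140 |
| 30 | 0.8 | 0.643 | 0.785 | 0.142 |
| 30 | 1.13 | 0.946 | 0.979 | 0.033 |
| 22.5 | 0.5 | 0.152 | 0.270 | 0.118 |
| 22.5 | 0.8 | 0.475 | 0.642 | 0.167 |
| 22.5 | 1.13 | 0.841 | 0.925 | 0.084 |

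Pooling the error variance over the four cells changes little: for d = 0.8, 0.660 against 0.795 at n = 30, and 0.496 against 0.656 at n = 22.5.

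**6. Precision.** With 30 per cell, the difference detectable with 80% power is 0.93 SD at 0.05/6 and 0.81 SD at 0.025. The normal critical values are 2.638 and 2.241. Their ratio is 1.18, so adjusted intervals are about 18% wider.

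**The case against.** The strongest reply is that the article never says the acupuncture-versus-sham contrasts will be tested at 0.05/6. A reader might infer that it does, but no divisor or list of pairs is printed. The two-sample tests or the repeated-measures analysis could carry the MoCA comparison without this adjustment. That stands, and the point is therefore conditional. It is still more than a detail left to an analysis plan: a multiplicity rule is stated, and applied to the only multi-group structure described it gives six pairs.

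A reader might also infer that the error rate is wrong. It is not. All-pairs Bonferroni controls type I error, and the cost is power and precision. Nor does the article propose to interpret a mixed pair.

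A third tempting reading is that 0.64 or 0.48 is the trial's power to show that acupuncture works. The documents do not support that. Under an equal arm effect of d = 0.8, a comparison pooled over genotype (48 v 48 at the planned 96) has power 0.97 at 0.05. The lower figures apply to each within-genotype contrast and rest on the assumed d.

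Finally, genotype comparisons are a stated aim for the microbiome, and the purpose in the Discussion is a difference in effect between genotypes, which no pair tests. Both objections stand and shape the fix.

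**Conclusion.** The point holds conditionally, as a cheap improvement and not as an error. The stated rule, read with the four-group design, implies six pairs at 0.0083, of which two are randomised and two cannot be attributed to either factor. If all six are tested and d = 0.8, narrowing the family to two raises power per randomised contrast from 0.64 to 0.79 with 30 per cell, and from 0.48 to 0.64 with 22.5 per cell. At d = 1.13 the gain is only 0.03 and 0.08 respectively. The conclusion rests on two assumptions that the article does not settle: that the Bonferroni family is all pairs of the four cells, and that f = 0.4 is purely an equal arm effect.

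**What to change.** Replace the general Bonferroni sentence, for MoCA, with a defined family:

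- The pairwise family is the two acupuncture-minus-sham contrasts, in carriers and in noncarriers, by Holm or at 0.025 each.
- The two pairs that differ in both arm and genotype are not tested.
- Carrier-versus-noncarrier contrasts within an arm are reported for MoCA as descriptive estimates with intervals.
- The carrier-versus-noncarrier comparisons in Faecal microbiome analysis stay as planned.
- Whether acupuncture works differently by genotype is judged by the arm-by-genotype interaction with its interval, not by setting one stratum's p-value against the other's. With equal cells and a common SD, its standard error is √(4/n) SD against √(2/n) SD for one stratum contrast, 1.41 times as large, so the interval will be wide.

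This takes about a sentence for the family and another for the interaction, with no new patients or data. It should be settled before anyone sees MoCA results by arm. The downside is that within-arm genotype contrasts on MoCA lose confirmatory status.

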## Results

Enrolment began in March 2021, and the total number of participants at the time of this writing is 98 patients. The final results will be published in 2023.

## Discussion

MCI is the prophase state of dementia and the key phase for early intervention. At present, there is no drug that can be used in the MCI stage. Acupuncture reflects the value of early intervention in MCI. The purpose of this study is to evaluate the difference in the curative effect of acupuncture on MCI patients with and without the *ApoE ε4* gene polymorphism and to explore the relationship between the acupuncture mechanism and changes in the intestinal flora. We hope to be able to provide assessable biomarkers associated with acupuncture treatment.

*ApoE* ε4 is associated with degeneration of brain capillary pericytes that maintain blood–brain barrier (BBB) integrity [8, 41]. *ApoE* ε4 carriers (ε3/ε4 or ε4/ε4 alleles) are distinguished from noncarriers (ε3/ε3) by BBB breakdown in the hippocampus and medial temporal lobe [8]. Disruption of the gut flora balance in pathogen-free mice has been linked to increased BBB permeability in the embryonic stage of development and in adults [42] as well as central nervous system abnormalities such as cortical myelination, hippocampal neurogenesis, cognitive function, and memory formation [43]. It has been suggested that systemic inflammation induced by compounds secreted by bacteria impairs the BBB and promotes neurodegeneration [44–46]. We hypothesize that specific types of microbiota contribute to *ApoE* ε4-associated breakdown of the BBB in patients with MCI and can serve as biomarkers for progression to AD.

EX-HN1 (Sishencong) and GV20 (Baihui) have the local effect of regulating brain function. Acupoints can regulate the brain network by increasing connections between cognitive-related regions, thereby improving cognitive function in MCI patients [47]. By improving brain function, acupoints further affect the movement, sensation, and secretion of the gastrointestinal tract through the descending pathway of the gut–brain axis and regulate the composition and behaviour of the gut microbiota [48]. The purpose of our research is to elucidate the relationship between acupoints and gut microbiota.

Clinically, acupuncturists treat patients individually based on their symptoms. As the fixed acupuncture program can reduce research deviation and is more conducive to promotion, we selected fixed acupoints.

This study has some limitations. The study was designed as a single-centre pilot study due to the lack of adequate preliminary studies. Second, some possible interfering factors (pathogenic genes) have not yet been considered.

## Conclusion

This study will explore the relationship among gut microbiota, AD susceptibility genes and acupuncture. It also aims to show that acupuncture can regulate the intestinal flora while improving cognitive function.

## Data Availability

Not applicable.

## List of abbreviations

MCI: mild cognitive impairment
AD: Alzheimer’s disease
ApoE: apolipoprotein E
ADL: activities of daily living
MMSE: Mini-Mental State Examination
GDS: Geriatric Depression Scale
BLAST: Basic Local Alignment Search Tool
OTU: operational taxonomic unit
USEARCH: ultrafast sequence analysis
LDA: linear discriminant analysis
BBB: blood–brain barrier
